### Theoretical approach

The theoretical framework of the intervention program is based on a psychosocial model of planned behavior change and the transtheoretical model (stages of change) at the individual level through systematic use of group processes [21]. The use of theory is supplemented by the practical experience obtained from Camp Fanoe.

### Day camp intervention arm

#### Family involvement

Family involvement had a central role in the DCIA on various levels. The families participated in an initial counseling session, with the aim of reaching family unanimity and securing the parents’ support of the children’s efforts to follow the designed program. Following this session, the children signed a *commitment contract* confirming their continuing involvement during the intervention. Parents received a handbook on dietary recommendations, a handbook concerning details in the camp program, and a pamphlet on child support. A parent council was founded before camp start to support parents in practical matters and augment participant involvement. Experiences from Camp Fanoe have revealed the positive influence of networking among parents and general parent involvement and support as a result of an active parent council. During the day camp the families were offered a dietary course led by a certified dietician. The course took place at the camp, where parents and children worked together to discuss healthy eating implementation in their families. The children were encouraged to commute actively if possible, preferably in smaller groups arranged according to residential area. Transportation was coordinated between the parents and the camp staff prior to the camp start.

### Content of the day-camp intervention arm

The day camps were located in the city of Odense, Denmark, and took place from mid-May to end of June in 2012 and 2013. The camp lasted for six consecutive weeks, seven days a week, and the children arrived every morning at 7 a.m. and left at 8.30 p.m. Except for commuting, the children typically stayed at home with their parents outside this time period. During a camp day the children were engaged in fun-based physical activity, sports, and health classes. Examples of activity classes include dancing, obstacle courses, teambuilding exercises, alternative ball games, adventure races, and more. All physical activity classes were planned and conducted by health professionals and specialist instructors and were primarily held in outdoor recreational facilities, such as soccer fields, basketball courts, and forest areas, within bicycling distance to the camp. Three hours of physical activity and sports were scheduled every day, and the classes were designed to reinforce motor skills, fitness, muscle strength, and confidence within the sporting environment. The planned exercise activities were both competitive and non-competitive, providing the children with both positive experiences in relation to physical activity and tools to cope with competitive situations in their normal environment. Every child was required to bring a bicycle to the camp. Besides scheduled physical activity the children were encouraged to stay physically active during breaks and leisure time. Six hours a week the children attended health classes with the purpose of increasing their knowledge on health issues such as the benefits of a healthy diet, sports participation, and increasing body awareness. The classes consisted of nutritional training, physiology, exercise, and goal setting. For this purpose appreciative inquiry (AI) was used to improve the potential for change within the children. This approach deals with inquiry into and dialogue about strengths, successes, values, hopes, and dreams related to lifestyle behaviors [22]. For at least one hour per day for five days a week, the children had time to focus on school work in order to follow the curricula of their classes in math, science, and Danish. The nutritional education consisted of a theoretical approach to the national Danish dietary recommendations in combination with personal guidance from the camp instructors during meals. At the camp, food was prepared and served according to the national Danish dietary recommendations [23]. The actual eating situation was supervised and guided by the camp instructors, but no calorie restriction was enforced.

### The subsequent family-based intervention

After the six-week intervention, a family-based (the participant and their parents/legal guardians) intervention consisting of four meetings during the subsequent 46 weeks was conducted targeting physical activity and dietary behavior. The meetings were led by trained school health nurses and instructors from the day-camp intervention. The following four themes were addressed during the four meetings: 1) healthy cooking and grocery shopping, 2) networking, 3) everyday physical activity, and 4) future challenges. The AI approach was applied in order to help the families handle the challenges related to behavioral changes. After the second meeting, an “activity and sports day” was arranged for the children by the camp instructors in order to give the children a supporting boost for the remaining intervention period. At all meetings, the families discussed and shared experiences related to the central topic of the meeting. The children had to be accompanied by at least one parent or legal guardian during these meetings.

### Standard intervention arm

As the Danish municipalities have no consensus in terms of how to offer help to obese children, no general standard intervention program can be used as comparison. Thus, it was decided to offer a shorter-term and less intensive intervention program compare to the day-camp group. This reflected a minimal effort to intervene in the children’s lifestyle and did not differ considerably from other initiatives being launched in Danish municipalities. This intervention consisted of one weekly fun-based physical activity session (1–2 hours duration) for six weeks, as well as a single health and lifestyle educational session for the parents, delivered by a dietician and physical activity specialist. The intervention program ended after six weeks.

### Measurements

A description of the measurements in the present study and time points of the assessments are presented in Table 1.

**Table 1 T1:** Description of parameters, applied methods, and time points of measuring in the OOIS

**Parameter**	**Method of measurement**	**Measurement time points**			
		** *Baseline* **	** *During camp* **	** *Follow-up 1 (post camp)* **	** *Follow-up 2 (post intervention)* **
**Anthropometrics**					
BMI and body composition	Height assessed without footwear and weight in underwear on a Soehnle Professional Medical electronic scale. Waist circumference was assessed between the lower costal margin and the iliac crest to the nearest 0.5 cm, at the end of a gentle expiration. Hip circumference was assessed at the level of the great trochanter. Dual energy X-ray absorptiometry (DEXA) was performed by an experienced operator on a GE Lunar Prodigy (GE Medical Systems, Madison, WI), equipped with ENCORE software (version 12.3, Prodigy; Lunar Corp, Madison, WI).	√		√	√
Pubertal development	Pubertal development was assessed according to Tanner by self-evaluation to avoid violating the child’s privacy.	√		√	√
**Motor skills and fitness**					
Manual dexterity, aiming and catching, and balance	The objective part of the Movement-ABC II test battery was applied.	√		√	√
Hand grip strength	Hand grip strength was assessed using a Smedley Dynamometer (max. 100 kg).	√		√	√
Jump height	Jump height was assessed by measuring tape using the Sargent jump protocol. The best of three jumps was noted.	√		√	√
Cardiorespiratory fitness	Cardiorespiratory fitness was assessed using a progressive bicycle ergometer protocol (Monarch Ergomedic 839e) until total exhaustion with indirect calorimetry (Innovision, AMIS 2001) and a Polar RS800CX heart rate monitor.	√		√	√
Arterial health	Blood pressure was assessed on the left upper arm with an automatic blood pressure monitor (Welch Allyn 300 series) after 5 minutes of rest in a sitting position. Resting heart rate was assessed by heart rate monitor (Polar RS800CX) during the ultrasound assessment as the child already was in a horizontal position and relaxed. Intima-media thickness and carotid elasticity were assessed in a lateral and a posterior position on the carotid artery with a GE LOGIQ e portable ultrasound machine with an attached 12 L-RS probe.	√		√	√
**Blood measurements**	After an overnight fast, blood samples were drawn in the morning from the antecubital vein (right arm). Participants were lying supine during blood collection. Samples for serum were left at room temperature for 30 minutes. Samples for plasma (EDTA) were centrifuged as soon as possible and put in the icebox (within one hour) before centrifugation. All samples were centrifuged at 2500G for 10 minutes. Then the samples were stored at -80°C until analysis.				
CVD risk factors	Fasting blood samples were analyzed for insulin, glucose, HbA1c, and lipids.	√		√	√
Growth factors	Fasting blood samples were analyzed for BDNF and FGF-21.	√		√	√
Adipokines and myokines	Fasting blood samples were analyzed for leptin, adiponectin, and irisin.	√		√	√
Inflammatory factors	Fasting blood samples were analyzed for CRP, TNF-α, and IL-6.	√		√	√
**Cognitive function**	The testing environment was comfortable and free from distraction. The cognitive tasks were administered individually in the following order:				
Visual memory	Rey Complex Figure Test (RCFT)	√		√	√
Attention and processing speed	Symbol Digit Modalities Test (SDMT)	√		√	√
Attention and executive function	Trail Making Test A & B (TMT A & B)	√		√	√
Executive function	Stroop Color and Word Test	√		√	√
**Child and parent surveys**					
Child’s lifestyle, perceived built environment and well-being	By computerized questionnaire. Test personnel helped with the questionnaire if needed.	√		√	√
Parent’s lifestyle and socio-economic status	By letter-distributed questionnaire.	√			√
Parent’s evaluation of child’s executive function	By Behavior Rating Inventory of Executive Function (BRIEF).	√			√
**Habitual physical activity**	Assessed by hip-worn accelerometer Actigraph GT3X + for 10 consecutive days for habitual physical activity, for seven consecutive days for estimated activity level during the day camp (SCIA only), and for two occurrences of fun-based physical activity for the SIA.	√	√		√
**Food intake**	Assessed by food registration for two whole days at the camp. For every meal the child had their food weighed and photographed for subsequent analyses of energy and nutrition content by trained and qualified personnel.		√		

### Outcomes

The screening process for overweight was performed by school nurses by assessing height and weight, thus making it relevant to use BMI as the primary outcome. Moreover, BMI and BMI z-score are frequently used as primary outcomes in comparable overweight interventions. To complement and validate the BMI assessment, body composition by DEXA scanning will be introduced. Furthermore, as a secondary outcome, a modified composite metabolic risk z-score will be calculated based on the definition by Andersen et al. [24]. This modified version contains summed z-scores for systolic blood pressure, triglycerides, total cholesterol/HDL ratio, insulin resistance (HOMA-IR), abdominal fatness by waist circumference, and aerobic fitness.

### Additional data collection

The study planned to be object for research on the development of motor skills and cognition as well (and potentially more), and thus a broad range of assessments was performed. The children’s self-reported lifestyle and wellbeing were obtained by computerized surveys. The parents answered questionnaires on their socioeconomic status, lifestyle, and estimated executive function of their children. Most measurements were conducted on three occasions: at baseline (post-randomization), immediately after the day camp, and at 12-month post-baseline measurements. To estimate the habitual physical activity level of the children, accelerometer-based activity monitors were applied for a minimum of seven consecutive days before and after the one-year intervention period. During the day camp, the physical activity level was assessed by the monitors, and the energy intake was assessed by photographic recording combined with weighing during two complete days.

### Training of test personnel

The test personnel for the physical tests were employed students or Ph.D. fellows enrolled at the university. Prior to the baseline testing, the test team was trained by experienced testers within the relevant areas. To gain sufficient experience, the personnel practiced the tests repeatedly on a comparable target group of overweight children prior to the testing.

### Data treatment and validation

During physical tests, the data was noted on test sheets. Shortly after completion, the data was typed into Epidata software by two independent researchers. The same was done for parent questionnaires. The two versions were compared for misspellings and typos, and subsequently corrected if needed. Fitness data, heart rate data, accelerometer data, children’s questionnaire data, and DEXA scan data were extracted from appurtenant apparatus and transferred into the applied statistical software (STATA version 12) for further analyses.

### Analysis plan and statistics

Analyses and reporting of the results will follow guidelines from *the CONSORT statement*[25]. Descriptive statistics will be used to present participation and retention rates, potential year group differences (2012 vs. 2013), and group differences in age, BMI, body fat percent, fitness level, parents’ socioeconomic status, and ethnicity. Similar analyses will be performed to search for any potential cohort differences (2012 vs. 2013). To compare the effect of the intervention between arms, mixed models will be applied. The primary analyses will be done according to the *intention-to-treat* principle. Supplementary, a sensitivity analysis will be performed according to a *per-protocol* analysis in children adhering to the intervention protocol, and thus strict registration of participation will be conducted. Predefined decision rules specify that accepted adherence to the camp intervention requires an attendance of 85% of the time (corresponding to 34/40 days) for the DCIA and 4 out of 6 activity sessions for the SIA. The following sub-group analyses across baseline characteristics have been determined *a priori*: age, gender, SES of the parent (s), ethnicity, habitual physical activity, and motor skills. These sub-group analyses will be performed by testing for interaction between the abovementioned variables and the treatment arm. Other sub-group and effect-mediating analyses conducted *post hoc* will be considered exploratory.

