## Methods

### Study design

The OOIS is a semi-blinded randomized controlled trial (RCT) with four measurement occasions. A population-based sample of overweight and obese children were invited to participate in either an already established resident overweight camp (Camp Fanoe) or the RCT. The participants choosing the RCT were randomly allocated to either the Day Camp Intervention Arm (DCIA) or the Standard Intervention Arm (SIA). The DCIA is a day camp lasting six weeks with a subsequent 46-week follow-up parent-supported intervention period. The SIA is a standard physical activity intervention consisting of one weekly activity class for six consecutive weeks.

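### The per-protocol attendance cut for the day-camp arm is set on 40 days, but the camp description gives 42, and the article does not explain the difference

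*Protocol article*

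**What the plan says.** The section on the analysis plan and statistics makes intention-to-treat the primary analysis and adds that "a sensitivity analysis will be performed according to a *per-protocol* analysis in children adhering to the intervention protocol". It then gives adherence rules that it describes as predefined. For the DCIA, accepted adherence "requires an attendance of 85% of the time (corresponding to 34/40 days) for the DCIA". The standard intervention arm has its own rule, based on activity sessions, which is not at issue here.

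The section on the content of the day-camp arm describes the schedule to which that attendance refers: "The camp lasted for six consecutive weeks, seven days a week, and the children arrived every morning at 7 a.m. and left at 8.30 p.m". It places the camps in the calendar only loosely, saying that they "took place from mid-May to end of June in 2012 and 2013". The study design section also gives the length in weeks: "The DCIA is a day camp lasting six weeks with a subsequent 46-week follow-up parent-supported intervention period".

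The article gives no start or end dates. It mentions no days off, no public holidays, and no arrival, departure or test days left out of the attendance count.

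**The concern.** An adherence rule stated as a percentage needs a denominator. Here the denominator in the rule differs by two days from the one implied by the description of the camp. For most children this makes no difference. For a child who attended 34 or 35 days it may: on a 40-day base the child meets 85%, and on a 42-day base the child does not.

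The rule decides who enters the per-protocol set, and the article says that participation will be strictly registered for this purpose. A predefined rule is meant to remove discretion over membership. If the denominator is still unsettled when the set is drawn, someone may have to settle it with outcome data in hand. A report might also describe the set as having at least 85% attendance when the cut actually applied was lower.

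**Working it through.** **Inputs**
- Threshold: 85% of the time, equated to 34 of 40 days (Analysis plan and statistics).
- Camp length: six consecutive weeks, seven days a week (Content of the day-camp intervention arm); six weeks also in Study design.
- Children randomised to the DCIA: 59 (Abstract, Methods).

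**Step 1. Reproduce the stated figure.** 34 / 40 = 0.850, and 0.85 × 40 = 34.0. The percentage and the day count agree exactly on a base of 40.

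**Step 2. Denominator from the camp description.** 6 weeks × 7 days = 42 days.

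**Step 3. Apply 85% to 42 days.** 0.85 × 42 = 35.7, so the smallest whole number of days that reaches 85% is 36.

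**Step 4. Compare attendance on the two bases.**

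| Days attended | Of 40 | Of 42 | Meets 34-day cut | Meets 85% of 42 days |
|---|---|---|---|---|
| 33 | 82.5% | 78.6% | no | no |
| 34 | 85.0% | 81.0% | yes | no |
| 35 | 87.5% | 83.3% | yes | no |
| 36 | 90.0% | 85.7% | yes | yes |

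Only the rows for 34 and 35 days differ.

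**Step 5. Could 34 come from rounding on a longer camp?** The smallest whole number of days reaching 85% is 34 when the camp has 39 days (0.85 × 39 = 33.15) or 40 days (34.0). With 41 days it is 35 (34.85), and with 42 days it is 36. Rounding up from 42 days therefore cannot produce 34, and the rule names 40 explicitly.

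**Step 6. Does the calendar settle it?** No. If mid-May is taken as 15 May (an assumption, as no date is given), the window to 30 June holds 17 + 30 = 47 days, which has room for 40 or 42.

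**The case against.** The best defence is that the rule is complete and correct as written. It gives a numerator, a denominator and a percentage, and the three agree. An analyst who follows it would apply 34 days; a cut of 36 appears nowhere in the article and is obtained only by carrying over a descriptive sentence from another section. That sentence may be a round description, while the analysis section is the only place that states a number of days. On that view 40 is the more specific figure and nobody is misclassified. The per-protocol analysis is also supplementary, and the article gives no attendance distribution that would show any child is affected.

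Much of this stands. The rule does not contradict itself, and no effect on an estimate has been shown. What remains is that the camp description is not vague about frequency: it says seven days a week and every morning, and no section accounts for the two missing days. A reader with only this article cannot tell which figure is to be corrected.

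Two stronger readings are tempting. One is that children below 85% are in fact being counted as adherent. The article does not support that as a plain statement, because it holds only if all 42 days count and 34 days is the cut applied. The other is that this is the only sensitivity analysis planned. It is the only one the article names, but a condensed article cannot show that there are no others.

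**Conclusion.** The inconsistency is real: a 40-day base in the adherence rule against a 42-day camp in the intervention description, with no explanation. It lies between sections and is not an arithmetic error within the rule.

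Its consequence is conditional. If 42 days were scheduled and countable, the 34-day cut is 81.0% attendance, two days short of an 85% rule. If 40 days were held or counted, the cut is correct and the camp description is what needs changing. The article does not decide between these.

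The size is modest under either branch. At most, the DCIA children with exactly 34 or 35 days change set. How many of the 59 that is cannot be known from the article, and it may be none. The primary intention-to-treat comparison of BMI does not depend on the rule. The point merits correction because it concerns the definition of an analysis set and costs almost nothing to put right, not because it threatens the main result.

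**What to change.** Before the per-protocol set is drawn:

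1. State how many camp days were scheduled and countable for attendance, separately for 2012 and 2013 if the two years differed.
2. Bring the intervention description and the adherence rule into line with that number. If it is 40, say why six full weeks yield 40.
3. Write the threshold as one day count that matches: at least 36 of 42, or at least 34 of 40.

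This takes a sentence or two. The article already plans to register participation, so no new data are needed. If the count turns out to be 42 and the cut moves to 36, any child with 34 or 35 days leaves the per-protocol set; if it is 40, membership does not change. The article places the last 12-month measurements in spring 2014, so on its own timetable the change could be made before those data are complete.

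### The per-protocol sensitivity analysis filters the two arms by unequal attendance rules and leaves out the 46-week family phase, so it is open to selection bias of unknown size and direction

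*Protocol article*

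**What the plan says.** All places are in the Methods of the Protocol article.

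- **Analysis plan and statistics.** Intention-to-treat is primary ("The primary analyses will be done according to the" intention-to-treat principle). The per-protocol analysis comes second: "Supplementary, a sensitivity analysis will be performed according to a" per-protocol approach.
- **The rule, same section.** It is fixed in advance and worded for the camp: "Predefined decision rules specify that accepted adherence to the camp intervention requires" 85% of the time, given as 34 of 40 days, "for the DCIA and 4 out of 6 activity sessions for the SIA".
- **Content of the day-camp intervention arm.** "The camp lasted for six consecutive weeks, seven days a week", and "the children arrived every morning at 7 a.m. and left at 8.30 p.m".
- **Standard intervention arm.** One session of 1 to 2 hours a week for six weeks and one educational session for parents. Nothing follows after week six.
- **The subsequent family-based intervention.** The DCIA then has a family-based "intervention consisting of four meetings during the subsequent 46 weeks was conducted". The adherence rule does not mention these meetings.
- **Study aims and hypothesis; Sample size and randomization.** The trial tests a one-year programme and is powered for a 12-month difference of 1.5 BMI points.

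**The concern.** A per-protocol set is chosen after randomisation. If the arms are filtered by different rules, the remaining children may differ in motivation, and randomisation no longer balances them. Here the higher percentage is attached to the far heavier demand: days of 13.5 hours against one short session a week.

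The rule also stops at week six, while the comparison of interest is at 12 months. A DCIA child who attends no family meeting still counts as adherent to a one-year programme.

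Because the analysis is called a sensitivity analysis, readers will tend to take agreement with intention-to-treat as corroboration. A contrast that can move without any treatment effect cannot provide that.

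**Working it through.** **1. The stated thresholds.** 34/40 = 85.0%, which reproduces the article's figure. 4/6 = 66.7%. The gap is 18.3 percentage points. Six sessions cannot give 85% exactly: 0.85 × 6 = 5.1, so the neighbours are 5/6 = 83.3% and 6/6 = 100%.

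**2. The denominator.** Six weeks × 7 days = 42 days, not 40. 34/42 = 81.0%, and 85% of 42 is 35.7, that is 36 days.

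**3. The SD.** The article gives 2.3 beside the 1.5-point difference. Reading it as SD 2.3 gives n = 2 × (1.960 + 0.842)² × 2.3² / 1.5² = 36.9, so 37 per arm, as stated. SD 2.3 is used below.

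**4. Chance of qualifying at the same attendance** (binomial, independent days; attendance levels assumed):

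| Attendance | 34/40 | 4/6 | 5/6 |
|---|---|---|---|
| 80% | 0.29 | 0.90 | 0.66 |
| 85% | 0.61 | 0.95 | 0.78 |
| 90% | 0.90 | 0.98 | 0.89 |
| 95% | 1.00 | 1.00 | 0.97 |

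**5. What drives the sign.** Suppose adherence has correlation r with lower 12-month BMI, there is no true effect, and shares qD and qS qualify. Then

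spurious difference towards the camp = 2.3 × r × [m(qD) − m(qS)], with m(q) = φ(z)/q and z the (1 − q) normal quantile.

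For qD = 0.6 and qS = 0.9: m = 0.644 and 0.195, so 2.3 × 0.3 × 0.449 = 0.31 at r = 0.3, and 0.10 at r = 0.1. With 80% qualifying in both arms it is 0. With the shares swapped it is 0.10 to 0.31 against the camp.

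**6. Simulation with the article's own rules.** Inputs assumed: logit of daily attendance = a + M, M standard normal, a = 2.5, 2, 1.5, 1 in both arms; correlation r between M and lower BMI; no treatment effect. Kept if at least 34 of 40 days (DCIA) or 4 of 6 sessions (SIA). Entries in the last three columns are BMI points towards the camp; runs vary by about 0.01.

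| Typical attendance | DCIA kept | SIA kept | r = 0.1 | r = 0.3 | r = 0.3, SIA cut 5/6 |
|---|---|---|---|---|---|
| 92% | 79% | 95% | 0.06 | 0.18 | 0.10 |
| 88% | 63% | 90% | 0.09 | 0.28 | 0.17 |
| 82% | 45% | 82% | 0.13 | 0.39 | 0.25 |
| 73% | 28% | 70% | 0.17 | 0.50 | 0.34 |

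Against the 1.5-point target this is 4% to 11% at r = 0.1 and 12% to 33% at r = 0.3. A 5/6 cut leaves more than half of it (0.10/0.18 = 56%; 0.34/0.50 = 68%).

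**7. Lower attendance in the SIA** (r = 0.3, typical DCIA attendance 88%):

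| Typical SIA attendance | Logit gap | SIA cut 4/6 | SIA cut 5/6 |
|---|---|---|---|
| 73% | 1.0 | 0.11 towards | 0.04 against |
| 62% | 1.5 | 0.00 | 0.18 against |
| 50% | 2.0 | 0.14 against | 0.34 against |

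The bias vanishes at a gap of about 1.5 logits and then reverses. In that region a 5/6 cut makes it worse.

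**The case against.** The strongest reply is that this is a supplementary analysis with rules fixed in advance, behind an intention-to-treat primary. That stands and limits the consequence. With 37 per arm the standard error is about 2.3 × √(2/37) = 0.53, so even the largest simulated bias is below one standard error.

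A reader might infer that the rule favours the camp by construction. The documents do not support this. They give no attendance data and no link between attendance and BMI. Equal attendance propensity is an assumption, and lower SIA attendance is plausible: camp children signed a commitment contract and had coordinated transport, and families knew their allocation three weeks before baseline. Omitting the family meetings could dilute the camp effect rather than inflate it.

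Different cut-offs for different interventions are also not an error in themselves, and any per-protocol set shares the general weakness. This is fair as far as describing adherence goes. It does not make a between-arm contrast of differently filtered children unbiased.

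Finally, the article is condensed, and a rule for the meetings may stand in the full protocol. But the rule the article does fix is presented as the predefined one and ends with the camp.

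**Conclusion.** The point holds in a limited form. The per-protocol sets are defined by unequal rules (85% against 67%) and take no account of the 46-week phase. The contrast is therefore open to selection bias whose size and direction cannot be known from the article. Bias towards the camp is most plausible if a smaller share of DCIA than SIA children qualify: about 0.06 to 0.17 BMI points at r = 0.1 and 0.18 to 0.50 at r = 0.3, given equal attendance propensity and no true effect. It is nil at r = 0, and near zero or reversed if SIA attendance is sufficiently lower. The correlations and attendance levels are assumptions.

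The primary analysis is not affected. What fails is the use of the per-protocol result as corroboration. Separately, the 40-day denominator and the camp description do not agree. There may be a reason, but the article gives none.

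**What to change.** 1. Keep intention-to-treat as primary.
2. Add a complier-average (instrumental-variable) estimate on all randomised children, with randomised arm as instrument. Define the exposure as receipt of the DCIA programme including the family meetings, not camp days alone, since the meetings may act on BMI by themselves.
3. State the exclusion restriction and its weakness here: children who attend in part may still benefit, which this estimate would credit to those counted as recipients. Its test of no effect rests on the same randomised comparison as intention-to-treat, so it gives the size of the effect among recipients, not separate evidence.
4. Label the per-protocol contrast descriptive, report the share qualifying in each arm, and do not read its agreement with intention-to-treat as confirmation.
5. Show a 5/6 cut in the SIA only as a further sensitivity check, since it does not reliably remove the bias. Adding a meeting criterion to the DCIA per-protocol set alone would deepen the asymmetry.
6. Reconcile the 40 days with the 42 implied by the camp description, and restate the percentage or the day count accordingly.

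The cost is one extra model on participation data that the plan already promises to register (assuming that this covers the meetings), and a wider interval. For illustration, if 60% received the programme, the standard error of 0.53 would become about 0.53/0.6 = 0.89.
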